### Recruitment {15}

Rheumatologists from the Maasstad Hospital will recruit patients for this trial. Rheumatologists from the EMC, LUMC, FGV and ASH will pre-screen patients and refer suitable subjects for recruitment to the Maasstad Hospital.

Assignment of interventions: allocation

### Sequence generation {16a}

Randomization will be performed using a computerized randomization procedure in Castor EDC [30]. Patients will be randomized in a 1:1 ratio using variable block sizes of two, four and eight patients, stratified for disease type (RA or PSA) to avoid imbalances between groups. The order of the block sizes is unknown to the researchers.

### Concealment mechanism {16b}

Because the study intervention involves a surgical procedure, allocation is not concealed and will be revealed to both the patient and the researcher upon randomization.

### Implementation {16c}

After confirmation that the informed consent forms have been signed by the patient and researcher, randomization will be performed in Castor EDC. The allocated study arm will be revealed simultaneously to the patient and researcher.

## Assignment of interventions: Blinding

### Who will be blinded {17a}

Patients, researchers, rheumatologists and surgeons will not be blinded because the study involves a surgical procedure which requires the patient to come to the operation theatre and which will leave signs of arthroscopic surgery that will be recognizable to the outcome assessors.

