#### Secondary outcomes

The following secondary outcome measures will be measured at baseline, 3 months, 6 months and 12 months (Table 1):Range of motion (ROM) of the wrist measured using a standard goniometer, including pronation, supination, ulnar and radial deviation, and palmar and dorsal flexionGrip strength of the wrist measured using a dynamometer (Saehan). Grip strength will be calculated as the mean of three attemptsNumeric Rating Scale (NRS) pain scale. A score of 0 indicates no pain, and a score of 10 indicates the worst possible painEULAR response rate and Disease Activity Score (DAS28)Resolution of synovitis measured by wrist ultrasound in grey scale and power Doppler mode (baseline and 3 months only)Wrist arthritis and joint destruction on standard (plain) radiographs of the wrist (baseline and 12 months only)Quality of life measured with the EuroQol 5D (EQ-5D-5L) questionnaireBlood parameters including erythrocyte sedimentation rate (ESR) and C-reactive protein (CRP) (part of the routine clinical care)Complications and subsequent treatment

**Table 1 Tab1:** Trial schedule according to the recommendation for interventional trial (SPIRIT) guidelines

	Enrolment	Allocation	Post-allocation					
Timepoint**	*14 days (*± *4 days) prior to intervention*	Intervention	*Week 2*	*Week 4*	*Week 6*	*Month 3*	*Month 6*	*Month 12*
Enrolment								
Eligibility screen	X							
Informed consent	X							
Allocation	X							
Interventions								
Arthroscopic synovectomy		X						
Intra-articular corticosteroid injection		X						
Assessments								
Questionnaires (PRWE, EQ-5D-5L, iMCQ, iPCQ)	X					X	X	X
Physical exam (including ROM, GS and DAS28)	X					X	X	X
Wrist ultrasound	X					X		
Plain wrist radiographs	X							X
Blood parameters (ESR, CRP)	X					X	X	X
NRS pain scores	X		X	X	X	X	X	X
Complications and secondary treatment			X	X	X	X	X	X
Cost-effectiveness analysis								X

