### Procedure for unblinding if needed {17b}

Because a surgical procedure is involved, the trial is not blinded. Therefore, an unblinding procedure is not indicated.

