Secondary outcomes include the EULAR response rate, reduction of synovitis on wrist ultrasound, progression of wrist arthritis on plain radiography and quality of life. DAS28 scores are used to determine the EULAR response rate, which measures responsiveness to anti-rheumatic treatment. The DAS28 is a composite measure of disease activity in rheumatic patients calculated by evaluating 28 joints for swelling and tenderness, combined with NRS pain scores and C-reactive protein levels in the blood. Wrist ultrasound, performed by one of two experienced rheumatologists, is used to measure the resolution of synovitis and is scored using the EULAR-OMERACT combined scoring system which combines grey scale and power Doppler mode [33]. Ultrasound has demonstrated greater sensitivity than clinical assessment and conventional radiography for detecting synovitis in RA target joints [34, 35]. Standard wrist radiographs will be graded using the modified Larsen grading system, which scores degenerative wrist arthritis and joint destruction on a score of 0 to 5, 5 indicating the most joint abnormalities [36, 37]. The EuroQol 5D (EQ-5D-5L) questionnaire is a widely used standardized questionnaire scoring overall quality of life using five different 5-level domains, on a scale from 0 to 100. It has been validated and translated to Dutch [38, 39]. A cost-effectiveness analysis will be performed based on medical costs and productivity loss (see the ‘Methods for additional analyses (e.g. subgroup analyses) {20b}’ section). The iMTA Productivity Cost Questionnaire is a standardized instrument for measuring and valuing health-related productivity losses and estimated societal costs based on educational level, job type and lost workdays [40]. The iMTA Medical Consumption Questionnaire (iMCQ) is a standardized instrument including questions related to frequently occurring contacts with health care providers, medication use and home care [40]. Medical resource prizes will be obtained from the Dutch Healthcare Authority [41]. From these costs, cost-effectiveness will be calculated in relation to quality-adjusted life years (QALYs) using the EQ-5D-5L (or PRWE) over a 1-year and 5-year span.

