### Limitations

Limitations of this study include the non-blinding of participants and observers, which is impossible because the intervention includes a surgical procedure. In addition, wrist arthroscopies will be performed by a surgeon skilled in wrist arthroscopy. External validity could be at risk for centres that lack this expertise. However, wrist arthroscopy is on the rise and could be accessible to most rheumatologists in the near future. Finally, we chose to exclude patients with a history of bDMARDs, because one of the aims is to evaluate to what measure bDMARD use can be prevented by synovectomy. Immunological profiling of synovial biopsies will also not be possible in patients exposed to previous bDMARD therapy because of permanent molecular alterations to synovial cells.

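### The reason given for not blinding observers does not reach the grading of plain radiographs, which could be masked to arm

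*Protocol article*

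**What the plan says.** Three sections of the protocol article deal with blinding, and none exempts an outcome.

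- Who will be blinded {17a}: "Patients, researchers, rheumatologists and surgeons will not be blinded because the study involves a surgical procedure". The section gives two grounds: the patient has to attend theatre, and the operation "will leave signs of arthroscopic surgery that will be recognizable to the outcome assessors".
- The section on unblinding, item {17b}, adds: "Because a surgical procedure is involved, the trial is not blinded".
- Limitations: the "non-blinding of participants and observers, which is impossible because the intervention includes a surgical procedure".

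Two secondary outcomes are imaging scores, described under Plans for assessment and collection of outcomes {18a}. For radiographs: "Standard wrist radiographs will be graded using the modified Larsen grading system", on a scale of 0 to 5, at baseline and 12 months. No reader is named and no masking is stated. For ultrasound: "Wrist ultrasound, performed by one of two experienced rheumatologists, is used to measure the resolution of synovitis", scored on the EULAR-OMERACT combined system at baseline and 3 months. Storage of the images, or scoring apart from the examination, is not described.

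**The concern.** The justification rests on what can be seen on the patient, but a radiograph grade is assigned from a film. If the reason does not apply to that reading, then calling observer blinding impossible is a wrong statement about one of the trial's outcomes, and a feasible safeguard is ruled out without cause.

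The stake is detection bias in a named objective. The abstract lists radiologic progress among the secondary objectives, and the Discussion argues that slowing progression could prevent long-term morbidity and expense. Larsen grading involves judgement, so a reader who knows the arm may lean one way. In a trial where the patient-reported primary outcome cannot be masked, a wrist-specific outcome that can be masked is worth protecting.

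**Working it through.** No calculation decides this point. The check is whether each stated ground for non-blinding applies to each kind of assessment.

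1. **Patient-reported outcomes (PRWE, NRS pain, EQ-5D-5L).** The patient knows whether an operation took place. The reason applies and masking is not feasible.
2. **Hands-on assessments (range of motion, grip strength, DAS28 joint counts).** The assessor sees the wrist. The reason given in {17a} applies.
3. **Ultrasound.** The plan reads "Resolution of synovitis measured by wrist ultrasound in grey scale and power Doppler mode (baseline and 3 months only"). One of two rheumatologists performs it, and {17a} names rheumatologists as unblinded. The operator sees the wrist at 3 months, so the reason applies to the examination as described. Only a later re-score of saved images could be masked, and saving is not mentioned.
4. **Plain radiographs.** The grade comes from the film. Intervention description {11a} describes four dorsal portals and removal of soft tissue and debris with a shaver. The routine procedure, as written, includes no implant and no bone resection, so nothing in it would be expected to show the arm on a 12-month film. One caveat is that ligament and fibrocartilage injuries found at arthroscopy are dealt with at the surgeon's discretion, so a trace in single patients cannot be excluded. For the generality of films neither stated ground applies.

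For item 4, then, the statement in Limitations is broader than the reason offered for it.

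**Effect on the primary analysis.** The sample size uses PRWE inputs only: difference 11.0, SD 15.0, correlation 0.1, α = 0.05 (taken as two-sided), power 90%. With baseline in the model the residual SD is 15 × √(1 − 0.1²) = 14.925, and n = 2 × (1.960 + 1.282)² × 14.925² / 11² ≈ 38.7, that is 39 per arm against the 38 stated. A simulation of the likelihood ratio test gives power 0.894 at 38 per arm. Allowing for 5% loss, 38 / 0.95 = 40 per arm, as stated. The plan's figure reproduces closely, and masked film reading changes none of its inputs.

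**Size of reader bias.** If a fraction p of wrists in one arm were moved by one grade, the mean would shift by p × 1 grade: from 0 at p = 0 to 0.2 at p = 1 in 5. The document gives nothing from which to choose p, so this only restates an assumption and is not used below.

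**The case against.** The best case against the point has four parts.

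- **The article is a condensed protocol.** It names no radiograph reader, and how films are read is detail that a full protocol may hold. This stands in part: a reader might infer that the films will be graded by someone who knows the arm, and the document does not say so. But the article does not merely omit masking. It answers the blinding item outright and says that blinding of observers cannot be done; a fuller document that provided for masked reading would contradict it.
- **Only secondary outcomes are involved, and the limitation is disclosed.** This is true. Neither imaging outcome is in the list of secondary outcomes for the mixed model in Statistical methods {20a}. Cross-over and treatment changes are allowed after 3 months, so masking would not make the 12-month films a clean comparison of the two procedures. This limits the weight of the point. Disclosure does not remove it, because the reason disclosed is wrong for this reading.
- **Ultrasound is different.** A reader might infer that ultrasound could be masked just as easily from stored images. The document does not support that: it describes no storage, and an unblinded operator would still choose which views to save. This objection stands, and the ultrasound part is conditional.
- **Masking is not free, and masking the time point is not essential.** Both stand. The document gives no cost and names no reader, so it cannot be said that no additional reader is needed. Knowing the visit affects both arms alike and does not by itself bias the comparison between them.

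**Conclusion.** The point holds for the radiographs. The grounds in {17a} cover patients, treating staff and assessors who see the wrist, and the unqualified claim in Limitations goes beyond them. Larsen grading at baseline and 12 months can be masked to arm within the design as written. This assumes that the routine arthroscopy leaves nothing on the film that identifies the arm, which fits the described procedure but is not stated.

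The reach is modest: one secondary outcome firmly, and ultrasound scoring only if images are saved. Two stronger conclusions should not be drawn. The first is that the primary result is at stake: the PRWE is self-reported by unblinded patients, and masked film reading would neither help nor harm it. The second is that a bias of some particular number of grades is to be expected: the document supports no figure. This is a low-cost improvement to a named objective and does not threaten the trial's main conclusion.

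**What to change.** 1. In Who will be blinded {17a} and in Limitations, limit the statement that blinding is not possible to patients, clinicians and hands-on assessments.
2. In Plans for assessment and collection of outcomes {18a}, state that baseline and 12-month radiographs will be de-identified and graded by a reader masked to arm, for example in one shuffled batch at the end of follow-up. Masking of the time point is optional.
3. If ultrasound images are saved, add a score masked to arm as a supportive reading, and say that this masks scoring but not acquisition.

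The cost is the work of coding and shuffling the films, and radiograph grades for the trial that become available only at the end. Whether another reader is needed depends on who grades the films now, which the article does not say. No visit, treatment, sample size or error rate changes, and because the films are already scheduled, the masked reading can still be adopted with recruitment under way.

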### Procedure for unblinding if needed {17b}

Because a surgical procedure is involved, the trial is not blinded. Therefore, an unblinding procedure is not indicated.

## Data collection and management

### Plans for assessment and collection of outcomes {18a}

Baseline data will be derived from the electronic patient record. Standard protocol for rheumatic patients in the Maasstad Hospital requires a 3-month follow-up with DAS28 scores, blood parameters and physical examination. In case of persistent wrist inflammation, regular wrist ultrasounds and yearly wrist radiographs are indicated. All laboratory tests, ultrasounds and radiographs will be performed in the Maasstad Hospital according to regular standards. NRS pain scores at 2, 4 and 6 weeks after the intervention will be obtained by phone call. Questionnaires will be sent to patients digitally using the Castor survey application [30]. All data will be collected with an electronic case report form (eCRF) in Castor EDC.

The primary outcome will be measured using the PRWE, which is a self-reported questionnaire that consists of 15 questions regarding pain and disability of the wrist when performing daily activities [31]. The highest score is 100 and indicates severe disability, and the lowest score is 0 and indicates no disability. The PRWE has been validated for patients with rheumatoid arthritis and for the Dutch language [27, 32]. Also, normative data and the minimal clinically important difference have been calculated for the PRWE [28, 29].

Secondary outcomes include the EULAR response rate, reduction of synovitis on wrist ultrasound, progression of wrist arthritis on plain radiography and quality of life. DAS28 scores are used to determine the EULAR response rate, which measures responsiveness to anti-rheumatic treatment. The DAS28 is a composite measure of disease activity in rheumatic patients calculated by evaluating 28 joints for swelling and tenderness, combined with NRS pain scores and C-reactive protein levels in the blood. Wrist ultrasound, performed by one of two experienced rheumatologists, is used to measure the resolution of synovitis and is scored using the EULAR-OMERACT combined scoring system which combines grey scale and power Doppler mode [33]. Ultrasound has demonstrated greater sensitivity than clinical assessment and conventional radiography for detecting synovitis in RA target joints [34, 35]. Standard wrist radiographs will be graded using the modified Larsen grading system, which scores degenerative wrist arthritis and joint destruction on a score of 0 to 5, 5 indicating the most joint abnormalities [36, 37]. The EuroQol 5D (EQ-5D-5L) questionnaire is a widely used standardized questionnaire scoring overall quality of life using five different 5-level domains, on a scale from 0 to 100. It has been validated and translated to Dutch [38, 39]. A cost-effectiveness analysis will be performed based on medical costs and productivity loss (see the ‘Methods for additional analyses (e.g. subgroup analyses) {20b}’ section). The iMTA Productivity Cost Questionnaire is a standardized instrument for measuring and valuing health-related productivity losses and estimated societal costs based on educational level, job type and lost workdays [40]. The iMTA Medical Consumption Questionnaire (iMCQ) is a standardized instrument including questions related to frequently occurring contacts with health care providers, medication use and home care [40]. Medical resource prizes will be obtained from the Dutch Healthcare Authority [41]. From these costs, cost-effectiveness will be calculated in relation to quality-adjusted life years (QALYs) using the EQ-5D-5L (or PRWE) over a 1-year and 5-year span.

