### Eligibility criteria {10}

#### Inclusion criteria

Patients must meet the following criteria to be eligible for the study:The patient is 18 years or older.The patient is able and willing to give written informed consent and is available for the entire study.Patients are diagnosed with RA, according to the revised 2010 ACR/EULAR Rheumatoid Arthritis Classification Criteria [20], *or* PsA, according to the CASPAR criteria [21]The patient is experiencing an exacerbation as reflected by an increase in DAS28 > 1.2 or > 0.6 if DAS28 ≥ 3.2 compared to the last DAS28 measurement (maximum 6 months before), and/or clinical assessment by a rheumatologist.The exacerbation is refractory to systemic cDMARDs for at least 3 months.Wrist arthritis is the predominant symptom.

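### DAS28 is defined with NRS pain as its patient-rated component instead of the patient's global rating, so one pain score feeds three secondary outcomes and the DAS28 and EULAR cut-offs are applied to a modified score

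*Protocol article*

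**What the plan says.** The section Plans for assessment and collection of outcomes {18a} gives the only definition of DAS28 in the article: "calculated by evaluating 28 joints for swelling and tenderness, combined with NRS pain scores and C-reactive protein levels in the blood". The sentence before it makes the response endpoint depend on this score: "DAS28 scores are used to determine the EULAR response rate, which measures responsiveness to anti-rheumatic treatment".

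The Secondary outcomes list contains NRS pain as one item and EULAR response with DAS28 as another. The only NRS described is a 0–10 pain scale: "A score of 0 indicates no pain, and a score of 10 indicates the worst possible" pain. The list does not say whether the patient rates the study wrist or pain overall. Table 1 enters DAS28 within "Physical exam (including ROM, GS and DAS28") at enrolment and months 3, 6 and 12, and gives NRS pain its own row. No section mentions a patient global rating.

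The statistical methods section {20a} analyses DAS28, EULAR response and NRS pain in the same way as the primary outcome.

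DAS28 also has a role at entry. One route to establishing an exacerbation is an "increase in DAS28 > 1.2 or > 0.6 if DAS28 ≥ 3.2 compared to the last DAS28 measurement" taken at most 6 months earlier. A rheumatologist's clinical judgement is offered as an additional or alternative route. On the population and the design: "Wrist arthritis is the predominant symptom", and "Patients, researchers, rheumatologists and surgeons will not be blinded".

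**The concern.** DAS28 is a named, standard index. Its patient-reported part is a global rating of health or disease activity. The definition in {18a} lists all four components and puts pain in that place. This is a stated definition, not a detail left to a fuller document.

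Two things follow.

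- **Overlap.** The same pain score becomes the NRS pain outcome, a term in DAS28 and, through DAS28, an input to EULAR response. Three favourable results could look like three pieces of evidence when part of each is one self-report from a patient who knows the treatment received.
- **Fit of the cut-offs.** The 0.6, 1.2 and 3.2 values in the entry rule, and the EULAR response categories, belong to the standard score. A pain-based score is a different quantity. If the earlier routine DAS28 used a global rating and the study value used pain, the entry comparison would mix two versions.

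At stake is the reading of two secondary endpoints. The article describes EULAR response as a measure of response to anti-rheumatic treatment, and systemic therapy is held constant for the first 3 months apart from exceptions. A DAS28 difference between arms at 3 months would naturally be taken as a change in overall disease activity, although pain relief alone could supply part of it.

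**Working it through.** **The plan's own figures.** The article prints no DAS28 weights, no EULAR response cut-offs and no DAS28 effect size, so there is no DAS28 figure to reproduce. Its one computed figure is the PRWE sample size. With SD 15.0 and correlation 0.1, the residual SD is 15 × √(1 − 0.1²) = 14.92. For a difference of 11, two-sided α = 0.05 (sidedness assumed) and 90% power, the normal approximation gives 39 per arm against the stated 38, and power at 38 is 89.5%. Then 38 / 0.95 = 40. The figure reproduces within tolerance, and DAS28 does not enter it.

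**Overlap, from the text alone.**

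1. NRS pain is a secondary outcome (Secondary outcomes).
2. NRS pain is a component of DAS28 ({18a}).
3. EULAR response is computed from DAS28 ({18a}).
4. All three are analysed between arms ({20a}).

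Hence a change in pain reaches all three. This step needs no outside source.

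**Size of the pain term.** Inputs:

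- Weight *w*, in DAS28 units per NRS point: 0.14, range 0.10–0.18. This is an assumption; the article gives none.
- Steps of 0.6 and 1.2, from the Inclusion criteria. They are used there for worsening at entry and serve here only as a yardstick.

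Shift in DAS28 from a pain change of Δ points with nothing else changing = *w* × Δ. Points needed to reach a step = step / *w*.

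| | *w* = 0.10 | *w* = 0.14 | *w* = 0.18 |
|---|---|---|---|
| 3-point fall in pain: *w* × 3 | 0.30 | 0.42 | 0.54 |
| as a share of 0.6 | 50% | 70% | 90% |
| points to reach 0.6 | 6.0 | 4.3 | 3.3 |
| points to reach 1.2 | 12 (off the scale) | 8.6 | 6.7 |

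Pain alone could plausibly cross the smaller step, but hardly the larger one.

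**Excess over the standard score.** The table assumes that global health does not move. If global health moves by a fraction *f* of the pain change, the shift due to the substitution is *w* × 3 × (1 − *f*). At *w* = 0.14 this is 0.42 for *f* = 0, 0.14 × 3 × 0.5 = 0.21 for *f* = 0.5, and 0 for *f* = 1. The documents give no basis for choosing *f*, so 0.42 is the upper end for a 3-point fall at that weight, provided global health does not move the opposite way.

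**The case against.** The strongest reply is that the sentence is a one-line gloss among several instrument descriptions, not an instruction to build a new index. DAS28 is routine at the hospital and study visits coincide with routine ones, so a correct score with a global rating may well be on record. The article prints neither the standard components nor their weights. In a population whose main complaint is the wrist, a global rating would partly follow wrist pain and is equally open to expectation in an unblinded trial. EULAR response overlaps with DAS28 under any definition. Table 1 does not split DAS28 into parts, not even the joint counts, so the absence of a global item there proves little.

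Most of this stands as a limit on size. It does not remove the point: the sentence is the only definition that someone building the case report form or analysing the data can follow from this article, and it names the wrong component. If the routine score is correct, the text still needs correcting, at almost no cost.

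Some stronger readings are tempting but unsupported.

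- A reader might infer that DAS28 would contain the treated wrist's pain. No section says which site the NRS rates.
- A reader might infer that 0–10 values would enter a 0–100 term unscaled and depress the score. Nothing in the article suggests this.
- A reader might infer that patients were wrongly admitted. The entry rule does not rest on DAS28 alone, since clinical judgement can also establish the exacerbation, and how the earlier DAS28 was calculated is not stated.

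**Conclusion.** The point holds as a defect in the definition of a secondary outcome that should be corrected. As written, DAS28 contains NRS pain where the named index has the patient's global rating. NRS pain, DAS28 and EULAR response then share a self-reported component in an unblinded trial, and the cut-offs are applied to a modified score.

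Under the assumed weight of 0.14 per NRS point (0.10–0.18), a 3-point fall in pain with global health unchanged shifts DAS28 by 0.42 (0.30–0.54), and about 4.3 points (3.3–6.0) reaches 0.6. The actual excess is smaller to the extent that global health moves with pain, and cannot be fixed from the article.

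The conclusion rests on the sentence in {18a} being followed literally and on the ordinary definition of DAS28, which the article does not print. The primary PRWE endpoint, its model and the sample size are untouched. The consequence for eligibility is limited by the clinical alternative.

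**What to change.** - In {18a}, define the score as DAS28-CRP with the patient's global health or disease-activity rating as the fourth component, and state that item's wording and scale.
- Take the rating from the routine DAS28 record, or collect it at the visits that already score DAS28: baseline and months 3, 6 and 12.
- Keep NRS pain as its own outcome and state whether it rates the study wrist or overall pain.
- Use the same DAS28 version for the current and the earlier value in the entry comparison.
- Where only pain was recorded, flag the score as modified and report it in a sensitivity analysis.

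The cost is a wording correction and at most one patient-reported item at existing visits. The one real drawback concerns patients already enrolled: if the global rating is not in their record, their DAS28 stays approximate and has to be labelled as such.

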## Abstract

**Background:**

Rheumatoid arthritis (RA) and psoriatic arthritis (PsA) are inflammatory diseases that often affect the wrist and, when affected, can lead to impaired wrist function and progressive joint destruction if inadequately treated. Standard care consists primarily of disease-modifying anti-rheumatic drugs (DMARDs), often supported by systemic corticosteroids or intra-articular corticosteroid injections (IACSI). IACSI, despite their use worldwide, show poor response in a substantial group of patients. Arthroscopic synovectomy of the wrist is the surgical removal of synovitis with the goal to relieve pain and improve wrist function. The primary objective of this study is to evaluate wrist function following arthroscopic synovectomy compared to IACSI in therapy-resistant patients with rheumatoid or psoriatic arthritis. Secondary objectives include radiologic progress, disease activity, health-related quality of life, work participation and cost-effectiveness during a 1-year follow-up.

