**Methods:**

This protocol describes a prospective, randomized controlled trial. RA and PsA patients are eligible with prominent wrist synovitis objectified by a rheumatologist, not responding to at least 3 months of conventional DMARDs and naïve to biological DMARDs. For 90% power, an expected loss to follow-up of 5%, an expected difference in mean Patient-Rated Wrist Evaluation score (PRWE, range 0–100) of 11 and *α* = 0.05, a total sample size of 80 patients will be sufficient to detect an effect size. Patients are randomized in a 1:1 ratio for arthroscopic synovectomy with deposition of corticosteroids or for IACSI. Removed synovial tissue will be stored for an ancillary study on disease profiling. The primary outcome is wrist function, measured with the PRWE score after 3 months. Secondary outcomes include wrist mobility and grip strength, pain scores, DAS28, EQ-5D-5L, disease progression on ultrasound and radiographs, complications and secondary treatment. Additionally, a cost-effectiveness analysis will be performed, based on healthcare costs (iMCQ questionnaire) and productivity loss (iPCQ questionnaire). Follow-up will be scheduled at 3, 6 and 12 months. Patient burden is minimized by combining study visits with regular follow-ups.

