## Objectives {7}

The primary objective of this study is to evaluate the effects of arthroscopic synovectomy of the wrist in therapy-refractory patients with RA or PsA compared to IACSI. The primary objective is to compare the improvement of wrist function 3 months after the intervention, measured using the Patient-Rated Wrist Evaluation (PRWE) questionnaire. The secondary objectives are to evaluate differences over a 12-month period in range of wrist motion, grip strength, DAS28 score, reduction of synovitis on wrist ultrasound, progression of joint destruction on wrist radiographs, blood inflammation parameters and overall quality of life. Additionally, complications, secondary drug treatment and secondary surgery will be evaluated. Finally, a cost-effectiveness analysis will be performed based on healthcare-related costs (using the iMCQ questionnaire) and loss of productivity (using the iPCQ questionnaire) over a 12-month period.

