### Outcomes {12}

#### Primary outcome

The primary outcome is the difference in wrist function, measured with the Patient-Rated Wrist Evaluation (PRWE) at 3 months compared to baseline. The PRWE is a measure of pain and wrist function in activities of daily living. The PRWE will be measured as a secondary outcome at 6 and 12 months.

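### The QALY statement offers the PRWE, as described a disability score without utility anchors, as a source of utilities, and sets a 5-year span that conflicts with the 12-month economic analysis stated elsewhere

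*Protocol article*

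**What the plan says.** The instruction for the effect side of the cost-effectiveness analysis is in the protocol article under Plans for assessment and collection of outcomes {18a}. Cost-effectiveness is to be expressed "in relation to quality-adjusted life years (QALYs) using the EQ-5D-5L (or PRWE) over a 1-year and 5-year span".

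The same section describes the two instruments. For the PRWE: "The highest score is 100 and indicates severe disability, and the lowest score is 0 and indicates no disability". The Primary outcome section adds: "The PRWE is a measure of pain and wrist function in activities of daily living". The EQ-5D-5L is described as "scoring overall quality of life using five different 5-level domains, on a scale from 0 to 100".

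On duration, the abstract's Background refers to "work participation and cost-effectiveness during a 1-year follow-up" and its Methods say: "Follow-up will be scheduled at 3, 6 and 12 months". Objectives {7} ties the economic analysis to healthcare costs and "loss of productivity (using the iPCQ questionnaire) over a 12-month period". In Table 1 the row beginning "Questionnaires (PRWE, EQ-5D-5L, iMCQ, iPCQ" is marked at enrolment and at months 3, 6 and 12. The cost-effectiveness row is marked at month 12 only.

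The Cost-effectiveness analysis subsection of {20b} computes a single ICER, the cost difference over the effect difference, once costs and utilities are available.

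**The concern.** A QALY is time weighted by a preference-based utility, on a scale where 0 stands for dead and 1 for full health. Naming the PRWE as an alternative source of QALYs treats a joint-specific disability score as if it were such a utility. A horizon longer than follow-up, given beside the 1-year horizon without qualification, reads as a second result of the same trial analysis.

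Cost-effectiveness is a named objective of the trial. An ICER built on a score that is not a utility, or on years in which nothing is measured, could be reported as a trial finding although the trial's data do not support it.

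**Working it through.** The plan gives no calculated figure to reproduce here. The check compares the instruction in {18a} with the instruments, the schedule and the ICER definition elsewhere in the article.

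**Step 1: does each instrument, as described, supply a utility?**

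| | Description in the article | What a QALY needs |
|---|---|---|
| PRWE | Wrist pain and function; 0–100; higher is worse. Properties cited: validation in RA and in Dutch, normative data, a minimal clinically important difference | Preference-based utility anchored at dead and full health |
| EQ-5D-5L | Five domains of five levels; scale given as 0 to 100 | The index (utility) value derived from the five domains |

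The PRWE description contains no value set and no mapping to utilities, and the scale runs in the opposite direction to a utility. The ICER subsection asks for utilities, so the PRWE option in {18a} does not meet the article's own requirement. The EQ-5D-5L can meet it, but through its index and not through a 0–100 number.

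**Step 2: does the horizon match the data?**

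Inputs: last scheduled EQ-5D-5L, PRWE, iMCQ and iPCQ at month 12 (Table 1); longer horizon 5 years = 60 months ({18a}).

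- Share of the 5-year span covered = 12 / 60 = 20%.
- Months without any scheduled measurement = 60 − 12 = 48, and 48 / 60 = 80%.

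The sections on horizon, side by side:

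| Place | Economic horizon |
|---|---|
| Abstract, Background | 1 year |
| Objectives {7} | 12 months |
| Table 1 | Questionnaires end, and analysis is marked, at month 12 |
| {18a} | 1 year and 5 years |

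Only {18a} goes past 12 months. The cost subsection of {20b} draws on hospital financial data and the two cost questionnaires and describes no projection.

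**Step 3: which results come directly from the scheduled data?**

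Two instruments × two horizons = 4 combinations.

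| | 1 year | 5 years |
|---|---|---|
| EQ-5D-5L | Yes: measured at 0, 3, 6 and 12 months, and the intervals 3 + 3 + 6 = 12 months cover the year | No: 48 months unmeasured |
| PRWE | No: no utility as described | No, on both counts |

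One of the four is directly obtainable.

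**The case against.** The strongest reply is that health-economic evaluations often use a horizon longer than follow-up, by modelling. A journal article condenses the full protocol, where such a model could be described. That is fair, and the absence of a model is not held against the plan here. A reader might infer that a 5-year result is impossible, but the documents support less than that: it cannot come from the trial data alone. Twelve months of costs and EQ-5D-5L data could feed a model. What remains is that {18a} states the 5-year span as on a par with the 1-year one, against the other sections, and does not call it modelled.

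It can also be said that the 12 months in Objectives {7} describe the window for collecting costs and do not cap the horizon. That reading is possible. The abstract, which attaches one year to cost-effectiveness itself, and the month-12 mark in Table 1 are the clearer evidence.

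A third reply is that the bracketed PRWE may be loose wording for a second effect measure, cost per PRWE change. That would be legitimate, but the sentence ties it to QALYs. Nor does the article say outright that the PRWE lacks utility weights; this follows from its description. A mapping function from PRWE to utilities cannot be ruled out from these documents, but none is mentioned.

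Four stronger readings are tempting and are not supported:

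- **Reversed sign.** A reader might infer that a better but costlier treatment would look dominated, because lower PRWE is better. That requires an unreversed score to be put into the ICER. No section says so, and {20b} asks for utilities.
- **QALYs inflated 100-fold.** The 0–100 range appears in a description of the questionnaire. Nothing says that number will be the QALY weight.
- **Instrument chosen after seeing the data.** The article does not say when or how the choice is made.
- **Cross-over after month 3.** It is permitted, but has no stated link to the instrument or the horizon.

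**Conclusion.** The point holds as an error in what {18a} states. As described in the article, the PRWE does not supply the utilities the ICER needs, and the 0–100 scale given for the EQ-5D-5L is not the QALY index. The 5-year span conflicts with the 1-year or 12-month horizon in the abstract, the objectives and Table 1. The trial data cover 20% of it, and it is not marked as an extrapolation.

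The conclusion assumes that a QALY requires a preference-based utility anchored at dead and full health, and that no follow-up beyond the schedule in Table 1 is planned. The 80% is the share of the horizon left unmeasured; it does not measure bias.

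The weight is moderate. The valid analysis, EQ-5D-5L over 1 year, is already contained in the same clause. The matter concerns a secondary economic analysis; the primary outcome and the sample size are untouched.

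**What to change.** In {18a}:

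1. State that QALYs are calculated from EQ-5D-5L index (utility) values at baseline, 3, 6 and 12 months, and correct the scale description to match.
2. Delete the bracketed PRWE alternative from the QALY statement. If a PRWE-based ratio is wanted, report it separately as cost per PRWE improvement, with the direction of improvement stated.
3. Delete the 5-year span, or label it as a model-based extrapolation separate from the trial result.

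The choice of value set and the details of the QALY calculation can stay in the analysis plan. The cost is a change of wording in one section. No new data, visits or patients are needed. The only loss is that a 5-year figure, if kept, can no longer be presented as a result of the trial itself.
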